**OSWESTRY DISABILITY QUESTIONNAIRE**

This questionnaire has been designed to give us information as to how your back or leg pain is affecting your ability to manage in everyday life. Please answer by checking **one box in each section** for the statement which best applies to you. We realise you may consider that two or more statements in any one section apply but please just shade out the spot that indicates the statement ***which most clearly describes your problem.***

**Section 1: Pain Intensity**

I have no pain at the moment

The pain is very mild at the moment

The pain is moderate at the moment

The pain is fairly severe at the moment

The pain is very severe at the moment

The pain is the worst imaginable at the moment

**Section 2: Personal Care (Washing, Dressing, etc.)**

I can look after myself normally without causing extra pain

I can look after myself normally but it causes extra pain

It is painful to look after myself and I am slow and careful

I need some help but can manage most of my personal care

I need help every day in most aspects of self care

I do not get dressed, wash with difficulty and stay in bed

**Section 3: Lifting**

I can lift heavy weights without extra pain

I can lift heavy weights but it gives me extra pain

Pain prevents me lifting heavy weights off the floor but I can manage if they are conveniently placed e.g. on a table

Pain prevents me lifting heavy weights but I can manage light to medium weights if they are conveniently positioned

I can only lift very light weights

I cannot lift or carry anything

**Section 4: Walking**

Pain does not prevent me walking any distance

Pain prevents me from walking more than 2 kilometres

Pain prevents me from walking more than 1 kilometre

Pain prevents me from walking more than 500 metres

I can only walk using a stick or crutches

I am in bed most of the time

**Section 5: Sitting**

I can sit in any chair as long as I like

I can only sit in my favourite chair as long as I like

Pain prevents me sitting more than one hour

Pain prevents me from sitting more than 30 minutes

Pain prevents me from sitting more than 10 minutes

Pain prevents me from sitting at all

**Section 6: Standing**

I can stand as long as I want without extra pain

I can stand as long as I want but it gives me extra pain

Pain prevents me from standing for more than 1 hour

Pain prevents me from standing for more than 30 minutes

Pain prevents me from standing for more than 10 minutes

Pain prevents me from standing at all

**Section 7: Sleeping**

My sleep is never disturbed by pain

My sleep is occasionally disturbed by pain

Because of pain I have less than 6 hours sleep

Because of pain I have less than 4 hours sleep

Because of pain I have less than 2 hours sleep

Pain prevents me from sleeping at all

**Section 8: Social Life**

My social life is normal and gives me no extra pain

My social life is normal but increases the degree of pain

Pain has no significant effect on my social life apart from limiting my more energetic interests e.g. sport

Pain has restricted my social life and I do not go out as often

Pain has restricted my social life to my home

I have no social life because of pain

**Section 9: Traveling**

I can travel anywhere without pain

I can travel anywhere but it gives me extra pain

Pain is bad but I manage journeys over two hours

Pain restricts me to journeys of less than one hour

Pain restricts me to short necessary journeys under 30 minutes

Pain prevents me from traveling except to receive treatment

**Section 10: Employment/Homemaking**

My normal homemaking/job activities do not cause pain.

My normal homemaking/job activities increase my pain, but I can still perform all that is required of me.

I can perform most of my homemaking/job activities, but pain prevents me from performing more physically stressful activities (eg lifting, vacuuming).

Pain prevents me from doing anything but light duties.

Pain prevents me from doing even light duties.

Pain prevents me from performing any job or homemaking chores

| **Health Questionnaire (EQ-5D-5L)** | |
| --- | --- |
| **Mobility**   - I have no problems in walking about - I have slight problems in walking about - I have moderate problems in walking about - I have severe problems in walking about - I am unable to walk about   **Self-care**   - I have no problems washing or dressing myself - I have slight problems washing or dressing myself - I have moderate problems washing or dressing myself - I have severe problems washing or dressing myself - I am unable to wash or dress myself   **Usual activities** (work, study, housework, family or leisure activity)   - I have no problems doing my usual activities - I have slight problems doing my usual activities - I have moderate problems doing my usual activities - I have severe problems doing my usual activities - I am unable to do my usual activities   **Pain / discomfort**   - I have no pain or discomfort - I have slight pain or discomfort - I have moderate pain or discomfort - I have severe pain or discomfort - I have extreme pain or discomfort   **Anxiety / depression**   - I am not anxious or depressed - I am slightly anxious or depressed - I am moderately anxious or depressed - I am severely anxious or depressed - I am extremely anxious or depressed   **NOTE:** To help people say how good or bad a health state is, we have drawn a scale (rather like a thermometer) on which the best state you can imagine is marked 100 and the worst state you can imagine is marked 0. | We would like you to indicate on this scale how good or bad your own health is today, in your opinion. Please do this by drawing a line from the box below to whichever point on the scale indicates how good or bad your health state is today.  9 0  8 0  7 0  6 0  5 0  4 0  3 0  2 0  1 0  100  Worst  imaginable  health state  0  Best  imaginable  health state  Your own  health state  today |

| Depression Anxiety and Stress Scale-21 | | | | |
| --- | --- | --- | --- | --- |
| Please read each statement and circle a number 0, 1, 2 or 3 which indicates how much the statement applied to you *over the past week*. There are no right or wrong answers. Do not spend too much time on any statement.  *The rating scale is as follows:*  0 Did not apply to me at all  1 Applied to me to some degree, or some of the time  2 Applied to me to a considerable degree, or a good part of the time  3 Applied to me very much, or most of the time | | | | |
|  | Not at all | Some of the time | A good part of the time | Most of the time |
| 1. I found it hard to wind down | 0 | 1 | 2 | 3 |
| 1. I was aware of dryness of my mouth | 0 | 1 | 2 | 3 |
| 1. I couldn’t seem to experience any positive feeling at all | 0 | 1 | 2 | 3 |
| 1. I experienced breathing difficulty (e.g. excessively rapid breathing, breathlessness in the absence of physical exertion) | 0 | 1 | 2 | 3 |
| 1. I found it difficult to work up the initiative to do things | 0 | 1 | 2 | 3 |
| 1. I tended to overreact to situations | 0 | 1 | 2 | 3 |
| 1. I experienced trembling (e.g. in the hands) | 0 | 1 | 2 | 3 |
| 1. I felt that I was using a lot of nervous energy | 0 | 1 | 2 | 3 |
| 1. I was worried about situations in which I might panic and make a fool of myself | 0 | 1 | 2 | 3 |
| 1. I felt that I had nothing to look forward to | 0 | 1 | 2 | 3 |
| 1. I found myself getting agitated | 0 | 1 | 2 | 3 |
| 1. I found it difficult to relax | 0 | 1 | 2 | 3 |
| 1. I felt down-hearted and blue | 0 | 1 | 2 | 3 |
| 1. I was intolerant of anything that kept me from getting on with what I was doing | 0 | 1 | 2 | 3 |
| 1. I felt I was close to panic | 0 | 1 | 2 | 3 |
| 1. I was unable to become enthusiastic about anything | 0 | 1 | 2 | 3 |
| 1. I felt I wasn’t worth much as a person | 0 | 1 | 2 | 3 |
| 1. I felt that I was rather touchy | 0 | 1 | 2 | 3 |
| 1. I was aware of the action of my heart in the absence of physical exertion (e.g. a sense of heart rate increase, heart missing a beat) | 0 | 1 | 2 | 3 |
| 1. I felt scared without any good reason | 0 | 1 | 2 | 3 |
| 1. I felt that life was meaningless | 0 | 1 | 2 | 3 |

| Pain Self-Efficacy Questionnaire | |
| --- | --- |
| Rate how confident you are that you can do the following things **at present** despite the pain. Circle one of the numbers on the scale under each item, where 0 = *Not at all confident* and 6 = *Completely confident*.  Remember this questionnaire is not asking whether or not you have been doing these things, but rather how confident you are that you can do them at present, **despite the pain.** | |
| 1. I can enjoy things, despite the pain | 0 1 2 3 4 5 6 Not at all Completely  confident confident |
| 1. I can do most of the household chores (e.g. tidying up, washing dishes, etc.) despite the pain | 0 1 2 3 4 5 6 Not at all Completely  confident confident |
| 1. I can socialise with my friends or family members as often as I used to do, despite the pain | 0 1 2 3 4 5 6 Not at all Completely  confident confident |
| 1. I can cope with my pain in most situations | 0 1 2 3 4 5 6 Not at all Completely  confident confident |
| 1. I can do some form of work, despite the pain (“work” includes housework, paid and unpaid work) | 0 1 2 3 4 5 6 Not at all Completely  confident confident |
| 1. I can still do many of the things I enjoy doing, such as hobbies or leisure activity, despite the pain | 0 1 2 3 4 5 6 Not at all Completely  confident confident |
| 1. I can cope with my pain without medication | 0 1 2 3 4 5 6 Not at all Completely  confident confident |
| 1. I can still accomplish most of my goals in life, despite the pain | 0 1 2 3 4 5 6 Not at all Completely  confident confident |
| 1. I can live a normal lifestyle, despite the pain | 0 1 2 3 4 5 6 Not at all Completely  confident confident |
| 1. I can gradually become more active, despite the pain | 0 1 2 3 4 5 6 Not at all Completely  confident confident |

| Pain Catastrophising Scale | | | | | |
| --- | --- | --- | --- | --- | --- |
| Everyone experiences painful situations at some point in their lives. Such experiences may include headaches, tooth pain, joint or muscle pain. People are often exposed to situations that may cause pain such as illness, injury, dental procedures or surgery.  We are interested in the types of thoughts and feelings that you have when you are in pain. Listed below are thirteen statements describing different thoughts and feelings that may be associated with pain. Using the scale, please indicate the degree to which you have these thoughts and feelings when you are experiencing pain. | | | | | |
|  | Not at all | To a slight degree | To a moderate degree | To a great degree | All the time |
| 1. I worry all the time about whether the pain will end | 0 | 1 | 2 | 3 | 4 |
| 1. I feel I can’t go on | 0 | 1 | 2 | 3 | 4 |
| 1. It’s terrible and I think it’s never going to get any better | 0 | 1 | 2 | 3 | 4 |
| 1. It’s awful and I feel it overwhelms me | 0 | 1 | 2 | 3 | 4 |
| 1. I feel I can’t stand it anymore | 0 | 1 | 2 | 3 | 4 |
| 1. I become afraid that the pain will get worse | 0 | 1 | 2 | 3 | 4 |
| 1. I keep thinking of other painful events | 0 | 1 | 2 | 3 | 4 |
| 1. I anxiously want the pain to go away | 0 | 1 | 2 | 3 | 4 |
| 1. I can’t seem to keep it out of my mind | 0 | 1 | 2 | 3 | 4 |
| 1. I keep thinking about how much it hurts | 0 | 1 | 2 | 3 | 4 |
| 1. I keep thinking about how badly I want the pain to stop | 0 | 1 | 2 | 3 | 4 |
| 1. There’s nothing I can do to reduce the intensity of the pain | 0 | 1 | 2 | 3 | 4 |
| 1. I wonder whether something serious may happen | 0 | 1 | 2 | 3 | 4 |

# Orebro Musculoskeletal Pain Screening Questionnaire

1. **How long have you had your current pain problem? Tick one**

0-1weeks [1] 1-2 weeks [2] 3-4 weeks [3] 4-5 weeks [4] 6-8 weeks [5]

9-11 weeks [6] 3-6 months [7] 6-9 months [8] 9-12 months [9] over 1 year [10]

1. **How would you rate the pain that you have had during the past week? Circle one.**

0 1 2 3 4 5 6 7 8 9 10

*No pain* *Pain as bad as it could be*

1. **How tense or anxious have you felt in the past week? Circle one. How much have you been bothered by feeling depressed in the past week? Circle one.**

0 1 2 3 4 5 6 7 8 9 10

*Absolutely calm and relaxed* *As tense and anxious as I’ve ever felt*

**4***.* **How much have you been bothered by feeling depressed in the past week? Circle one.**

0 1 2 3 4 5 6 7 8 9 10

*Not at all*  *Extremely*

1. **In your view, how large is the risk that your current pain may become persistent? Circle one.**

0 1 2 3 4 5 6 7 8 9 10

###### *No risk* *Very large risk*

1. **In your estimation, what are the chances that you will be working your normal duties in 3 months? Circle one (10-)**

0 1 2 3 4 5 6 7 8 9 10

###### *No chance* *Very large chance*

Here are some of the things which other people have told us about their pain. For each statement please circle one number from 0 to 10 to say how much physical activities, such as bending, lifting, walking or driving would affect your pain.

1. **An increase in pain is an indication that I should stop what I’m doing until the pain decreases.**

0 1 2 3 4 5 6 7 8 9 10

*Completely disagree* *Completely agree*

1. **I should not do my normal work with my present pain.**

0 1 2 3 4 5 6 7 8 9 10

*Completely disagree* *Completely agree*

Here is a list of 5 activities. Please circle the one number which best describes your current ability to participate in each of these activities (10-)

1. **I can do light work for an hour.**

0 1 2 3 4 5 6 7 8 9 10

*Can’t do it because Can do it without*

*pain problem pain being a problem*

1. **I can sleep at night.**

0 1 2 3 4 5 6 7 8 9 10 *Can’t do it because Can do it without pain problem pain being a problem*

**Insomnia Severity Index (ISI)**

For each question, please CIRCLE/TICK the number that best describes your answer.

*Please rate the CURRENT (ie last 2 weeks) SEVERITY of your insomnia problem(s).*

| **Insomnia Problem** | None | Mild | Moderate | Severe | Very severe |
| --- | --- | --- | --- | --- | --- |
| 1. Difficulty falling asleep | 0 | 1 | 2 | 3 | 4 |
| 2. Difficulty staying asleep | 0 | 1 | 2 | 3 | 4 |
| 3. Problems waking up too early | 0 | 1 | 2 | 3 | 4 |

**4. How SATISFIED/DISSATISFIED are you with your CURRENT sleep pattern?**

Very Satisfied Satisfied Moderately satisfied Dissatisfied Very Dissatisfied

0 1 2 3 4

**5. How NOTICEABLE to others do you think your sleep problem is in terms of impairing the quality of your life?**

Not at all noticeable A little Somewhat Much Very much noticeable

0 1 2 3 4

**6. How WORRIED/DISTRESSED are you about your current sleep problem?**

Not at all noticeable A little Somewhat Much Very much noticeable

0 1 2 3 4

**7. To what extent do you consider your sleep problem to INTERFERE with your daily functioning (eg daytime fatigue, mood, ability to function at work/daily chores, concentration, memory, mood etc) CURRENTLY?**

Not at all noticeable A little Somewhat Much Very much noticeable

0 1 2 3 4

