11. *Sleep quality:* The Insomnia Severity Index (ISI) will be used to assess sleep quality. The scale comprises 7 questions that assess current sleep problems that are rated on a 5-point Likert scale (‘0’ representing none or not at all and ‘4’ representing very much) ^[99]^. Total scores range from 0 to 28, with higher scores indicating worse insomnia severity ^[99]^. The ISI demonstrated good validity ^[99]^ and responsiveness ^[100]^ and has been used to assess sleep quality in individuals with LBP ^[101]^.
12. *Central sensitisation:* The Central Sensitisation Inventory (CSI) will be used to assess central sensitization symptoms. The CSI is a 25-point scale, rated on a scale of 0 (never) to 4 (always), with a score of more than 40 indicating the presence of central sensitization ^[102]^. The CSI is a useful and valid measure for screening patients with central sensitization symptoms ^[103]^ and has strong psychometric properties ^[104, 105]^
13. *Inflammatory symptoms:* The 4-item clinical inflammation score will be used to assess low back-related inflammatory symptoms. A positive clinical inflammation score of at least 3 of; constant symptoms, morning pain/stiffness greater than 60-min, short walking not easing symptoms and significant night symptoms will be used to inform clinical decision. This scale has been validated and achieved a sensitivity of 90.9%, a specificity of 92.9%, and predictive accuracy of 92.3% ^[106]^.
14. *Treatment acceptability:* The treatment Credibility Questionnaire will be used to determine the acceptability of each treatment approach ^[107]^. Treatment acceptability will be assessed at each follow-up visit via a 4-item questionnaire rated on a scale of 0-10, at this point, how logical does the treatment offered to you seem? At this point, how successful do you think this treatment will be in helping you with your back problem? How confident would you be in recommending this treatment to a friend who experiences similar problems? By the end of your treatment, how much improvement in your back condition do you think will occur? This questionnaire demonstrated high internal consistency and good test-retest reliability ^[107]^ and has been used in LBP trials ^[108, 109]^.
15. *Healthcare utilization:* A patient diary will be used to track healthcare utilization including imaging, medication, and other healthcare services ^[14,56]^.

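### ISI items 6 and 7 carry item 5's end labels, and Örebro item 3 contains a stray second question: two secondary-outcome forms to correct before use

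*Protocol*

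**What the plan says.** **ISI, as described.** Protocol Section 2.12, Secondary outcomes (sleep quality), says: "The scale comprises 7 questions that assess current sleep problems that are rated on a 5-point Likert scale". It gives the ends of the scale as 0 "representing none or not at all and ‘4’ representing very much", and adds: "Total scores range from 0 to 28, with higher scores indicating worse insomnia severity".

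**ISI, as printed.** In the patient-reported outcomes appendix, item 5 asks "How NOTICEABLE to others do you think your sleep problem is in terms of impairing the quality of your life" and offers labels running from not at all noticeable to very much noticeable. Item 6 asks "How WORRIED/DISTRESSED are you about your current sleep problem". Item 7 begins "To what extent do you consider your sleep problem to INTERFERE with your daily functioning". Under both items 6 and 7 the labels are "Not at all noticeable A little Somewhat Much Very much noticeable", scored 0 to 4, exactly as for item 5.

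**Örebro short form, as printed.** The stem of item 3 includes "How tense or anxious have you felt in the past week? Circle one. How much have you been bothered by feeling depressed in the past". Beneath it is one 0–10 scale, anchored from calm and relaxed to as tense and anxious as the patient has ever felt. Item 4 is the depression question again, with its own 0–10 scale.

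**Role.** Table 2 lists both instruments as secondary outcomes at weeks 0, 5, 10 and 26. Section 2.13 says patients fill in the questionnaires themselves at the clinic. Appendix 2 also names the Örebro as one of four questionnaires used to evaluate psychosocial barriers to recovery in the STOPS arm.

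**The concern.** These pages are the measuring instrument. A patient who is very worried about sleep, or whose daytime functioning suffers in ways that others do not see, finds no end label on ISI items 6 and 7 that matches the question. A patient who is calm but low in mood cannot answer both halves of Örebro item 3 with one circle.

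Section 2.12 supports both instruments by citing published measurement properties. Those properties belong to the instruments as validated, and they do not automatically extend to altered wording. Nor can an analysis plan repair the wording once patients have answered. The affected items enter the totals at every visit, including the baseline score for which the mixed model in Section 2.15 adjusts.

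**Working it through.** **Inputs.** Number of ISI items (7), points per item (0 to 4) and total range (0 to 28): Section 2.12. Item stems and labels: the appendix forms. Örebro: ten printed items, each with a top value of 10. The protocol states no total for the Örebro form, so 100 is derived here on the assumption of a simple sum.

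**1. Reproduce the stated ISI range.** 7 items × 4 points = 28, which matches Section 2.12.

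**2. ISI points exposed.** 2 items × 4 points = 8, and 8 / 28 = 28.6%. The remaining 28 − 8 = 20 points come from items 1 to 5, whose labels fit their stems.

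**3. Compare stems with labels in the ISI.**

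| Item | Asks about | End labels printed | Fit |
| --- | --- | --- | --- |
| 5 | Noticeability to others | Noticeable | Yes |
| 6 | Worry or distress | Noticeable | No |
| 7 | Interference with functioning | Noticeable | No |

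The three middle labels, the 0–4 numbers and the direction of scoring fit all three items. The mismatch is the word noticeable at the two ends of items 6 and 7. Section 2.12 describes the ends without that word, so the form also departs from the protocol's own text.

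**4. Örebro points exposed.** 10 items × 10 = 100. Item 3 carries at most 10, and 10 / 100 = 10%. Its anchors correctly answer its first question, on tension and anxiety. The second question is surplus, because item 4 asks it with a suitable scale. This is a different fault from the one in the ISI.

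**5. Text-extraction fault?** Unlikely. Nothing is missing or scrambled: complete but wrong words stand under two ISI stems, and a complete extra question stands inside Örebro item 3.

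**6. After correction.** No stated figure changes. The ISI remains 7 × 4 = 28, and the Örebro form remains at ten items.

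**The case against.** The strongest reply is that these are proofreading slips with little consequence. The ISI stems are intact and their key words are capitalised, the middle labels and numbers work, and Section 2.12 provides a research assistant to help patients with the forms. Most patients may answer the stem and ignore the odd end label. Both arms use the same forms at the same visits, and both instruments are secondary. Much of this stands, and it limits the point in four ways.

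- A reader might infer that 8 of the 28 ISI points are invalid, or that items 5 to 7 all measure noticeability. The documents do not support this. They hold no data on how patients read the labels, so 8 points is a ceiling on what is exposed.
- A reader might infer that depressed mood is counted twice in the Örebro total. That is conjecture, since the item 3 scale offers only answers about calm or tension.
- A reader might infer that item 3 can change a patient's STOPS subgroup. Appendix 2 requires an Örebro score greater than 105 for the subgroup with no identifiable pathoanatomical disorder, but the printed form cannot exceed 100. Item 3 as printed therefore cannot carry anyone across that threshold. The threshold and the form need to be reconciled as a separate matter. What remains is the assessment of psychosocial barriers, where the Örebro is one of four instruments.
- A reader might infer between-group bias. Nothing in the forms favours either arm.

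The reply does not remove the defect. Patients answer these pages directly, and the help of a research assistant does not replace correct printed wording.

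**Conclusion.** The point holds as a low-severity correction. ISI items 6 and 7 have end labels that belong to item 5, exposing up to 8 of 28 points (28.6%). Separately, Örebro item 3 contains a redundant depression question, exposing at most 10 of 100 points. The expected effect is extra measurement noise, together with weakened reliance on the validity cited in Section 2.12, for two secondary outcomes. The loss of precision cannot be estimated from the documents. Neither form bears on the Oswestry.

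This rests on three assumptions: that the appendix forms are the ones handed to patients, that the same wording is used in both arms and at every scheduled visit, and that the Örebro total is the plain sum of ten items.

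**What to change.** Before the forms are used:

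1. Make the end labels of ISI item 6 refer to worry and those of item 7 to interference. Take the exact words from the source instrument, because newly composed anchors would leave the same doubt about validity.
2. Delete the depression sentence from Örebro item 3 and keep it as item 4 only. Check that page against its source as well.
3. If enrolment has begun, record for each patient and visit which form version was completed, so that the analysis can take account of it.

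The cost is two reprinted pages and, if recruitment is under way, one extra data field. Scoring ranges, visit schedule and sample size are unaffected.
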